#### Impact of motor coordination on daily living

Parent report of child coordination difficulties interfering with daily life will be assessed with the revised Developmental Coordination Questionnaire (DCDQ-2007) [66], which assesses motor difficulties in individuals from 4 to 15 years of age. It has 15-items divided into three subscales: Control During Movement, Fine Motor/Handwriting and General Coordination, and uses a 5 point Likert scale ranging from 1: 'not at all like your child', to 5: 'extremely like your child'. The DCDQ-2007 is self-administered by parents, comparing their child's motor performance with that of their peers. Using translated versions of the DCDQ-2007 a correlation between test and retest of r = .94 was found (p < 0.001; n = 35) [67]. Factor analysis has verified the three subscales of the DCDQ-2007 explaining 79% of the variance [68], and concurrent validity has been demonstrated with a significant correlation of r = -.55 between the total score on the DCDQ-2007 and the original MABC [68].

#### Physical activity

Time spent in sedentary, light and moderate to vigorous intensity PA, as well as total movement, will be assessed over 7 days using an Actical accelerometer worn on the hip. The Respironics Actical is the most widely used and validated accelerometer in studies of children and adolescents [69]. Seven days of accelerometer measurement are recommended for the purposes of acceptable measurement of moderate to vigorous PA [70]. Total weekly activity as well as weekend activity and after school weekday activity will be assessed. Children will keep a brief diary recording accelerometer wear times and PA to assist with accelerometer data quality control and processing.

#### Attitudes to Physical Activity

Attitudes to PA will be assessed using the revised version [71] of the Physical Activity Enjoyment Scale [72]. Internal consistency, test-retest reliability and construct validity has been demonstrated [71,73,74].

#### Mental Health

Harter's Self-Perception Profile for Children [75] will assess self-perceptions across domains of Scholastic Competence, Social Acceptance, Athletic Competence, Physical Appearance and Behavioural Conduct, and it also includes a subscale designed to evaluate global self-worth that assesses self-esteem independent from the competence domains. It has been validated in samples of children from a wide range of cultural backgrounds, including in Australian children and has high levels of internal consistency ranging from .74 to .92 [75].

Spence Children's Anxiety Scale [76] assesses anxiety symptoms in children and consists of six subscales, namely panic attack and agoraphobia, separation anxiety disorder, social phobia, physical injury fears, obsessive compulsive disorder, and generalized anxiety disorder. This self report questionnaire consists of 45 items, 38 assessing specific anxiety symptoms and the remaining six items serve as positive 'filler' items in order to reduce negative response bias. Children are asked to indicate frequency with which each symptom occurs on a four-point scale ranging from Never (scored 0) to Always (scored 3). A total SCAS score is obtained by summing scores of the 38 anxiety symptom items. The scale has high internal consistency for the total score as well as for each subscale, with satisfactory test-retest reliability [77,78].

The Short Moods and Feelings Questionnaire [79] is a self report screening tool to assess depression in children and adolescents aged 8 to 16, that covers areas such as affective, vegetative and cognitive symptoms of depression. This asks the child to rate depressive symptoms in the past 2 weeks on a Likert scale ranging from 0 to 2, with possible responses of "not true," "sometimes true," and "true". It has 3-week and 3-month test-retest reliabilities of .84 and .80, respectively [80], high internal consistency [80] and validity with depressive diagnoses derived from standardized diagnostic interviews [81].

### Procedure

Following screening, participants will perform baseline assessments at the research centre after informed consent/assent from parent and child. Baseline assessments will include all measures described including laboratory biomechanical measures and questionnaires. Participants will be fitted with the accelerometer for wearing at home for the following week and receive check phone calls reminding the child to wear the accelerometer over the next week and to complete the activity diary. Half the participants will then be randomly allocated to the active electronic game conditions and half to the no electronic game (waitlist/normal care) condition by selection of an opaque sealed envelope. Randomisation will be balanced to equal numbers of boys and girls in both initial condition groups. A research officer (RO) will visit the home after one week and collect the accelerometers and instruct parent and child in the game condition. This will involve either removal of all active electronic games or setting up active electronic game equipment and instructing parent and child in its use. Follow-up phone calls will be made regularly to check participation, whether active game equipment is working correctly and electronic game exposure. Towards the end of the each condition the RO will visit again to set up the accelerometer assessments. After 16 weeks the child and parent will repeat assessments at the research centre. The RO will visit the participants and set up the other game condition. After 16 weeks in the other game condition the same assessments will occur. The family structure including number, age and sex of siblings will be recorded, and the behaviour of siblings during the trial will be assessed at debriefing interview. Accelerometer assessment will be scheduled to avoid school and public holidays where possible. Individualised reports will be provided to participants.

### Trial flow

Figure 4 provides an overview of the trial flow. Following recruitment, screening and consent and baseline assessments, participants are randomised to an order of electronic game conditions. Participants are setup in their first condition and are assessed at the end of the 16 week condition. Participants are then set up in their second condition for 16 weeks, again with assessment occurring at the end of the condition.

**Figure 4 F4:**
[figure not shown]
**Trial flow chart showing cross-over design and assessment points**.

### Analysis

To examine hypothesis 1 (that motor coordination will be improved when children have access to active electronic games) changes from baseline in laboratory biomechanical and MABC-2 outcomes following both conditions will be compared with a repeated measures ANCOVA analysis with sex as a covariate. A critical alpha level of 0.01 will be used to balance type 1 and type 2 errors.

To assess hypotheses 2, 3, 4, 5 (that parent reports of motor coordination in daily living, physical activity and sedentary behaviour, attitudes to physical activity and measures of mental health will improve when children have access to active electronic games) changes from baseline in outcomes following both conditions will be compared with a repeated measures ANCOVA analysis with sex as a covariate. A critical alpha level of 0.01 will be used to balance type 1 and type 2 errors.

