**Methods:**

This cross-over randomised and controlled trial will examine whether motor coordination is enhanced by access to active electronic games and whether daily activity, attitudes to physical activity and mental health are also enhanced. Thirty children aged 10-12 years with poor motor coordination (≤ 15^th ^percentile) will be recruited and randomised to a balanced ordering of 'no active electronic games' and 'active electronic games'. Each child will participate in both conditions for 16 weeks, and be assessed prior to participation and at the end of each condition. The primary outcome is motor coordination, assessed by kinematic and kinetic motion analysis laboratory measures. Physical activity and sedentary behaviour will be assessed by accelerometry, coordination in daily life by parent report questionnaire and attitudes to physical activity, self-confidence, anxiety and depressed mood will be assessed by self report questionnaire. A sample of 30 will provide a power of > 0.9 for detecting a 5 point difference in motor coordination on the MABC-2 TIS scale (mean 17, sd = 5).

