### Electronic game use may have a negative impact on normal motor development

Normal motor development requires maturation of neural and muscular systems plus the opportunity to practise fine and gross motor skills, with studies on children with impoverished or enriched motor environments providing evidence for the importance of practice [13]. Gross motor experiences are usually associated with physical activity (PA) (defined as the movement of the limbs and torso by muscle activity resulting in energy expenditure). There is evidence that increased PA can provide the practice necessary to improve gross motor skill development in children with normal motor development [14]. However there are concerns amongst researchers and parents that electronic game playing reduces children's PA.

Traditional electronic game interfaces can provide motor experience, but fine rather than gross. Yuji [15] reported evidence that electronic games improved children's fine motor performance. In a review, Whitcomb [16] found electronic game playing lead to enhanced eye-hand coordination, dexterity and fine motor ability and increased reaction and movement speeds in elderly subjects and Rosser et al. [17] found a dose response relationship between video game experience and laproscopic surgery training performance (both speed and accuracy).

In contrast, traditional electronic game playing probably does not provide gross motor experience, and may lead to a decline in gross motor skill. In an epidemiological study of 1,600 five-year-olds we found that computer use did displace vigorous PA on weekends reducing overall gross motor experience [18] and suggesting a potential vicious cycle.

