## Methods/design

### Design and Aims

This study will use a cross over randomised controlled trial to assess the impact of active electronic game use on motor coordination and physical and mental health correlates in children with DCD by:

1) Comparing change in motor coordination over 16 weeks when children use active electronic games or no active electronic games. We hypothesise that motor coordination will improve more when children use active electronic games.

2) Comparing change in parent reports of motor coordination during activities of daily living over 16 weeks when children use active electronic games or no active electronic games. We hypothesise that parent reports of motor coordination will improve more when children use active electronic games.

3) Comparing change in physical activity and sedentary behaviour over 16 weeks when children use active electronic games or no active electronic games. We hypothesise that moderate/vigorous physical activity will increase and sedentary time will decrease more when children use active electronic games.

4) Comparing change in attitudes to physical activity over 16 weeks when children use active electronic games or no active electronic games. We hypothesise that attitudes to physical activity will improve more when children use active electronic games.

5) Comparing change in child reports of mental health over 16 weeks when children use active electronic games or no active electronic games. We hypothesise that mental health will improve more when children use active electronic games.

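### The cross-over analysis compares a 16-week with a 32-week change from one baseline and names no period or order term: no bias at equal orders, but an inflated standard error and lost power

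*Protocol article*

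**What the plan says.** The trial is a two-period cross-over with 16 weeks in each condition. Under Methods in the Abstract, children will "be assessed prior to participation and at the end of each condition". Trial flow confirms the second half: "Participants are then set up in their second condition for 16 weeks, again with assessment occurring at the end of the condition". The Procedure section uses the word baseline for the assessments made before randomisation. It describes no new baseline before the second condition other than the assessment that ends the first. It also says that half the children start in each condition, with the sexes balanced between the two starting groups.

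For hypothesis 1 the Analysis section takes "changes from baseline in laboratory biomechanical and MABC-2 outcomes following both conditions" as the outcome, and these "following both conditions will be compared with a repeated measures ANCOVA analysis with sex as a covariate". The same model is stated for hypotheses 2 to 5. Sex is the only covariate named.

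The first aim, under Design and Aims, reads "Comparing change in motor coordination over 16 weeks when children use active electronic games or no active electronic games". The other four aims use the same 16-week wording.

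**The concern.** Two things do not fit together.

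- **The quantity.** A change from the pre-trial baseline spans 16 weeks for whichever condition comes first and 32 weeks for whichever comes second. The aims describe 16 weeks for both.
- **The model.** In a two-period cross-over, the nuisance effect that does not cancel within a child is the shift between periods. The article itself makes such a shift plausible. The children are 10 to 12 years old, and the Background says "Normal motor development requires maturation of neural and muscular systems". The same tests are given three times. The period length is fitted to the school calendar, so the two periods fall at different times of year. Sex is constant within a child and cannot remove a shift of this kind.

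At stake are the standard error and power of the condition comparison in all five hypotheses and, if the two orders finish with unequal numbers, a bias in the estimate.

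**Working it through.** **Inputs from the Sample section.** 30 children; effect 5 points on the MABC-2 Total Impairment Score; SD 5 within a child between time points; alpha 0.01; stated power 0.9027.

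**Reproducing the stated power.** SD of a within-child difference = 5 × √2 = 7.07. Standard error = 7.07/√30 = 1.291. Then 5/1.291 = 3.873, and 3.873 − 2.576 = 1.297, which gives 0.9027 (two-sided, normal approximation). The plan's figure is reproduced. The same comparison by paired t test gives 0.858 with 29 df, and 0.856 with 28 df once a period term is fitted. Sex is left out of these calculations.

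**What the stated contrast estimates.** Let Y0, Y16 and Y32 be a child's three scores, τ the effect of condition and P the mean shift from week 16 to week 32 that is not due to condition.

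- Active games second: (Y32 − Y0) − (Y16 − Y0) = Y32 − Y16, with mean τ + P.
- Active games first: (Y16 − Y0) − (Y32 − Y0) = Y16 − Y32, with mean τ − P.

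Y0 cancels in both. P does not; its sign depends on the order.

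**Equal orders, 15 and 15.** The mean of all differences is τ + P(15 − 15)/30 = τ, so there is no bias. The sample variance of the differences now contains the gap between the orders. Its expectation is

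50 + P² × 4·n1·n2/(N(N − 1)) = 50 + P² × 900/870.

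The mean difference still has true variance 50/30, so the ordinary t test divides by a standard error that is too large. To obtain power, the mean is taken as normal with variance 50/30, and 29s²/50 as non-central chi-square with 29 df and non-centrality 30P²/50. Simulation agrees to within about 0.005. P is an assumption throughout, because the documents give no value.

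| Assumed P (points) | Estimated SD of difference | True type I error | Power, no period term | Power, period term |
|---|---|---|---|---|
| 0 | 7.07 | 0.010 | 0.858 | 0.856 |
| 2 | 7.36 | 0.008 | 0.83 | 0.856 |
| 3 | 7.70 | 0.005 | 0.80 | 0.856 |
| 5 | 8.71 | 0.002 | 0.68 | 0.856 |

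(The type I error at P = 3 is 0.0054; simulation runs put it between 0.005 and 0.006.)

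**Unequal completers.** Bias = P(n1 − n2)/N, where n1 counts completers who had active games second. The splits are assumed, as no drop-out is stated. At 15 v 12 the bias is 3/27 = 0.11 × P, which is 0.22, 0.33 and 0.56 points for P = 2, 3 and 5. At 15 v 11 with P = 5 it is 5 × 4/26 = 0.77. With a period term the bias is zero at any split.

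**The case against.** The strongest defence is that the planned design protects the estimate. Orders are allocated in equal halves, so the period shift averages out and the test rejects too rarely, not too often. This stands. A reader might infer from the 16-week against 32-week mismatch that the treatment effect is biased or that false positives are likely. At equal orders neither follows. Even at a severe assumed split of 15 v 9, simulated type I error reaches only about 0.012.

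The size of P is also unknown. A value of 5 means a drift over one period as large as the effect judged important. The Sample section describes age norms for the MABC-2 standard score, which may absorb some growth in that measure if it is the score analysed. Accelerometry is scheduled away from holidays where possible. These points stand as limits. But age norms do not remove practice or season, and none is described for the two path-length primary outcomes.

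A smaller SD might seem to make matters worse. Applying a test-retest reliability of 0.75 to an SD of 5 gives an SD of the difference of 5 × √(2 × 0.25) = 3.54, and the standard error then grows by a larger proportion. Yet power for 5 points stays at or above 0.996 even at P = 5. The 0.75 also belongs to the original MABC, not to the MABC-2.

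A reader might further infer that children without a second assessment are dropped, or that the coding of sex distorts the condition test. The article fixes neither a missing-data rule nor a coding, so neither is a finding.

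Last, the article is condensed, and an unseen analysis plan may carry the term. That is possible. But the Analysis section names a model and its covariate for every hypothesis, and what it names does not match the aims.

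**Conclusion.** The point holds as a matter of precision and consistency. The stated model leaves the period shift in the error term. At equal orders there is no bias, but the test is conservative, and for the Total Impairment Score power falls from about 0.86 to about 0.83, 0.80 or 0.68 if the shift is 2, 3 or 5 points. These figures rest on the plan's SD of 5 at each time point, two-sided alpha 0.01 and 30 complete pairs. The loss for the other outcomes has the same cause but cannot be quantified from the documents. Bias arises only with unequal completers and is small against 5 points at modest imbalance.

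If baseline was meant as the start of each period, the mismatch in duration would go, but the period term would still be absent and the wording would still need correcting. Carry-over is a separate matter that a period term does not address. This is a should-fix, because the remedy is nearly free and the model as stated gives wrong standard errors whenever a period shift exists.

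**What to change.** For all outcomes, add period and randomised order to the stated model. Within the repeated measures ANCOVA, enter order as a between-child factor with its interaction with condition; in a two-period design that interaction is the period effect. A mixed model with condition, period and sequence is equivalent for this purpose, so replacing the ANCOVA is not required.

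Then reconcile Design and Aims with Analysis so that both name one quantity: the period-adjusted difference between conditions at the end of each 16-week period.

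The cost is one or two sentences and one degree of freedom. If there is no period effect, power goes from 0.858 to 0.856, a loss of about 0.2 percentage points.

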## Discussion

Children's increasing use of computers and especially electronic games may reduce their exposure to the large movement activities necessary for normal motor development and engagement in physical activity. Children with Developmental Coordination Disorder may be especially adversely affected. Persuading children to stop playing computer games is unlikely to be successful. However changing the nature of the movements they use when playing games may reduce the negative impact and potentially provide positive gains in motor ability, motor confidence and overall physical activity levels for children with normal and impaired motor development.

### Implications

This project will be the first to assess the longitudinal impact of providing VR electronic games to children with impaired motor development. The knowledge gained from this study will allow us to understand the potential of active VR games to provide children with the motor development and physical activity necessary for a healthy start to life.

## Abbreviations

ANCOVA: analysis of covariance; DCD: developmental coordination disorder; DCDQ: developmental coordination disorder questionnaire; MABC2: movement assessment battery for children - 2; MAND NDI: McCarron assessment of neuromotor disorder neurodevelopmental index; PA: physical activity; RO: research officer; SCAS: Spence children's anxiety scale; TGMD: test of gross motor development; TIS: total impairment scale; VR: virtual reality.
